### Statistical analysis

A sample size of 254 women (127 women per arm) was predefined to show the noninferiority of the experimental group (pessary) versus the reference group (progesterone), assuming a proportion of preterm birth (before 34 weeks) of 6 % and 12.4 %, respectively, with a noninferiority margin of 4 %, a 2.5 % one-sided alpha level, a statistical power of 80 % and a drop-out rate of 5 %.

Statistical analysis will be based on the intention-to-treat principle and a sensitivity analysis using the per-protocol subset for the main outcome will be used for sensitivity purposes. The noninferiority hypothesis will be tested by estimating treatment rate differences against the noninferiority margin. The survival function and the median (95 % confidence interval (CI)) time to delivery will be estimated by means of the Kaplan-Meier method and treatment effects will be compared using the log-rank test and hazard ratios (HR) (95% CI) will be taken from the Cox model. The rest of the variables will be analyzed using the Fisher’s exact test to compare categorical data, the t-test for continuous variables and the Mann- Whitney test for ordinal and non-normally distributed variables.

The analysis will be performed using SAS v9.2, or a newer version, software (SAS Institute Inc., Cary, NC, USA), and the level of significance will be set at 5 % (two-sided).

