Therefore, considering that the risk of prematurity is inversely proportional to cervical length, cervical measurement constitutes a method of screening for use in pregnant women who are asymptomatic before 24 weeks [15–17]. For decades, different types of therapeutic intervention have been explored in order to decrease preterm births, including primary prevention measures (all pregnant women), secondary prevention measures (only in women at risk) or tertiary prevention measures (initiated after the delivery process has started) [18]. A recent review concluded that there was insufficient evidence to provide sound recommendations for clinical practice in approximately half of the evaluated interventions [19]. Nevertheless, according to several trials and systematic reviews, two strategies, vaginal progesterone [20–28] and silicon cervical pessary [29–32], have been shown to be effective at decreasing the rate of spontaneous delivery before 34 weeks of gestation in at-risk women who have a short cervix.

Progesterone is a key hormone during gestation that has uterus-relaxing effects. Low levels of progesterone are associated with a high grade of cervix maturation and, consequently, a shorter cervical length and a higher risk of spontaneous delivery. The administration of progesterone supplements decreases preterm delivery in women with a short cervix [20–23] and in pregnant women with a history of preterm births [25, 26].

In March 2012, Romero et al. published a meta-analysis [27], which explored whether the use of vaginal progesterone in asymptomatic women whose ultrasound showed a short cervix (under 25 mm) in the second trimester reduced the risk of preterm birth and improved neonatal morbidity and mortality.

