### Randomization

Consecutive eligible patients are randomly allocated in a 1:1 ratio to one of the two treatment groups: vaginal progesterone or cervical pessary. The randomization sequence is computer generated (by EpiDat program). It is protected and it is managed exclusively by the Clinical Pharmacology Unit at University Hospital Puerta de Hierro - Majadahonda, which has no role in recruitment. The investigators receive the patient’s identification (ID) number and the assigned treatment by a central phone call, after having been informed that a new patient has entered into the trial. An auditable registry of the date and time of inclusion, patient ID number and treatment assignment is stored in the sponsor’s records.

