### Study outcomes

The primary outcome measure is the proportion of spontaneous preterm birth before 34 weeks of gestation. The secondary outcomes are the following: proportion of spontaneous preterm birth before the 37th and 28th weeks, the rate of premature rupture of membranes before 34 weeks, the neonate’s weight at birth, the rate of fetal intrauterine mortality during the treatment period, the rate of neonatal morbidity and mortality, the need for hospitalization and tocolysis treatment, the rate of chorioamnionitis during the third term, symptomatic vaginal infections during the treatment period and the proportion of participants with adverse events.

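### The primary rate difference names no covariate although cervical length is measured in every woman before treatment; a standardised risk difference would be a modest efficiency gain

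*Protocol article*

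**What the plan says.** - **Endpoint** (Study outcomes): "The primary outcome measure is the proportion of spontaneous preterm birth before 34 weeks of gestation".
- **Primary test** (Statistical analysis): "The noninferiority hypothesis will be tested by estimating treatment rate differences against the noninferiority margin". No covariate is named. The other comparisons in the section (log-rank, Fisher, t-test, Mann-Whitney) are unadjusted, and the Cox model is given without covariates.
- **Design figures** (Statistical analysis): "A sample size of 254 women (127 women per arm) was predefined to show the noninferiority", "assuming a proportion of preterm birth (before 34 weeks) of 6 % and 12.4 %, respectively" for pessary and progesterone, "with a noninferiority margin of 4" percent, "a 2.5 % one-sided alpha level", 80% power and 5% drop-out.
- **Allocation** (Randomization): women are "randomly allocated in a 1:1 ratio to one of the two treatment groups" from a computer-generated central list. No stratification factor is named.
- **Prognostic role of cervical length** (Background): "considering that the risk of prematurity is inversely proportional to cervical length, cervical measurement constitutes a method of screening".
- **Measurement** (Study population and trial development; Table 2): length is measured at the routine eligibility scan, and cervicometry is ticked again at Visit 0. Obstetric history is also baseline data. Table 1 excludes only women with three or more premature labours, so history can vary within the trial.
- **Abbreviations**: CMH (Cochran-Mantel-Haenszel), a stratified method, is defined but not used in the text shown.

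**The concern.** The variable that defines eligibility, and that the protocol presents as the main marker of risk, is recorded in every woman. As described, it plays no part in the allocation or in the primary estimate. With a binary outcome and few events, adjusting for a strong baseline predictor removes some random variation from the estimated difference. At stake is a little precision in a trial planned at exactly 80% power. The trial is also open-label, so it helps to fix in advance which estimate, crude or adjusted, is the confirmatory one.

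**Working it through.** **Inputs.** From the Statistical analysis section: rates of 6% (pessary) and 12.4% (progesterone), margin 4 percentage points (absolute, because the test is on a rate difference), one-sided alpha 2.5%, power 80%, drop-out 5%. The strength of cervical length as a predictor among women at or below 25 mm is not in the documents. It is assumed here as an odds ratio (OR) per SD shorter, from 1.0 to 3.0, the same in both arms, with length normally distributed.

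**Step 1: reproduce the plan's sample size (crude difference, unpooled variance).**

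n per arm = (1.960 + 0.842)² × [0.06 × 0.94 + 0.124 × 0.876] / (0.04 + 0.064)² = 7.85 × 0.16502 / 0.010816 = 119.8, so 120.

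Drop-out: 120 / 0.95 = 126.3, so 127 per arm and 254 in total. This matches the plan exactly, so the design does not rely on adjustment.

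**Step 2: standard error and power of the crude difference at 120 per arm.**

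SE = √(0.16502 / 120) = 3.71 points. Distance to the margin = 6.4 + 4 = 10.4 points, or 10.4 / 3.71 = 2.80 SE. Power = Φ(2.80 − 1.96) = 80.1%.

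Expected events = 120 × 0.06 + 120 × 0.124 = 7.2 + 14.9, about 22.

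**Step 3: large-sample variance of the standardised risk difference.**

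Variance = {E[p₁(1 − p₁)] + E[p₀(1 − p₀)]} / n + Var(p₁ − p₀) / (2n), where p₁ and p₀ are the risks given length under pessary and progesterone, with intercepts set so that the marginal rates stay at 6% and 12.4%.

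| Assumed OR per SD | SE (points) | Power | Equivalent n per arm before drop-out |
|---|---|---|---|
| 1.0 | 3.71 | 80.1% | 120 |
| 1.5 | 3.68 | 80.6% | 119 |
| 2.0 | 3.63 | 81.7% | 116 |
| 2.5 | 3.57 | 82.9% | 112 |
| 3.0 | 3.52 | 84.1% | 108 |

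**Step 4: does the gain survive with about 22 events?** Simulation at 120 per arm gave adjusted-to-crude variance ratios of about 1.00 (OR 1.5), 0.97 (OR 2) and 0.92 (OR 3). The large-sample ratios are (3.68/3.71)² = 0.98, (3.63/3.71)² = 0.96 and (3.52/3.71)² = 0.90, so the realised gain is slightly smaller than the table suggests. In a simulation of 4,000 trials per setting, power (crude against adjusted) was 82.4% against 81.8% at OR 1.5, 82.0% against 82.6% at OR 2, and 82.7% against 86.2% at OR 3.

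**Step 5: type I error at the margin (12.4% against 16.4%).** In the same simulation, one-sided error was 2.5 to 2.9% crude and 2.3 to 2.6% adjusted (Monte Carlo SE about 0.25 points). A further simulation gave 2.4 to 2.8% crude and 2.5 to 2.8% adjusted. Neither method shows material inflation.

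**Step 6: chance imbalance.** The SE of the between-arm difference in mean length is √(2/120) = 0.129 SD. An imbalance of that size moves the crude difference by about 0.4 points (OR 1.5), 0.7 (OR 2) or 1.0 (OR 3). As a share of the crude variance this is (0.4/3.71)² = 1%, (0.7/3.71)² = 4% and (1.0/3.71)² = 7%. These shares are close to the variance savings in Step 4, because imbalance is one of the components of the crude SE.

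**The case against.** The strongest reply is that the article does not say the difference is unadjusted. It is a condensed account, a rate difference can be stratified or standardised, and covariates and stratification factors are often left to the full protocol or SAP. The unused CMH entry may even point to a stratified analysis. This stands as a limit on certainty. A crude difference remains the natural reading, because the sample size comes from the crude formula and no comparison in the section names a covariate. But a reader who takes it as established that no adjustment is planned goes further than the text.

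The second reply is that nothing is wrong with a crude difference, and that stands in full. A reader might infer that chance imbalance in cervical length is an added threat: at OR 2 per SD, an imbalance of 0.25 SD shifts the estimate by about 0.25 × 0.693 × 0.09 × 0.91 = 1.4 points, a third of the margin. But 0.25 SD is about two standard errors of the imbalance, so it is uncommon, and such variation is already in the crude confidence interval. Nor does an SE close to the margin show weakness, because planned power rests on the 10.4-point distance in Step 2.

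Third, restricting entry to 25 mm or less may flatten the gradient, and the Background's statement supports screening rather than prediction within that range. This also stands, and it is why the lower end of the assumed range must be taken seriously.

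Finally, Table 2 places cervicometry and randomisation at Visit 0 without an order, and the list of data collected before randomisation does not mention cervicometry. The Visit 0 value is therefore not clearly a baseline value; the eligibility scan is.

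**Conclusion.** The point holds as a low-cost efficiency recommendation. As described, the primary test uses no covariate and the allocation no stratification, although a predictor that the protocol itself relies on is available in every woman before treatment. A standardised risk difference would use that information and keep the 4-point margin on its own scale, with no type I error penalty seen in simulation.

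The size is modest: about 0 to 4 power points for assumed ORs of 1.0 to 3.0 per SD, and practically nothing at 1.5 or below. No figure in the documents says where in that range the truth lies, so the lower sample sizes in the table should not be quoted as a saving the trial would achieve. The documents do not support reading this as an error, a bias or a shortfall in power. The conclusion also depends on the full protocol or SAP not already specifying adjustment or stratification.

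**What to change.** State in the analysis plan, before outcome data are compared by arm, that the primary estimate is the standardised (marginal) risk difference from a logistic model with treatment and pre-randomisation cervical length as a continuous term. Use the eligibility-scan value, or the Visit 0 value only if it is confirmed to precede allocation. Prior preterm birth (yes/no) may be added. Obtain the 95% confidence interval by the delta method or bootstrap and compare its upper limit (pessary minus progesterone) with 4 points. Report the crude difference as a sensitivity analysis.

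The cost is a change of wording and slightly more analysis work; the data are already collected and no further women are needed. The downside is a model resting on about 22 events, so covariates should stop at one or two. If the full protocol or SAP already names an adjusted or stratified estimate, leave it as it is.

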### Organization of the trial

PESAPRO is a noncommercial trial organized by the Obstetrics and Gynecology Department and the Clinical Pharmacology Unit of the University Hospital Puerta de Hierro - Majadahonda. The sponsor role is taken by [name]. The medical coordinator of the trial is [name]. The Clinical Pharmacology Unit oversees the methodological and organizational aspects of the study. Since 2014, the study has been receiving support from the Spanish Clinical Research network (SCReN) for regulatory and administrative support, monitoring, data management and pharmacovigilance. The PESAPRO study group comprised of all clinical investigators at the participating centers and the collaborators from the Clinical Pharmacology Unit.

#### Coordination and conduct of the trial

The study is coordinated by the Obstetrics and Gynecology Unit and the Clinical Pharmacology Unit (Appendix 2). Three investigator meetings have been held in order to review the study protocol and data collection in the electronic case report form (eCRF). Additionally, after the necessary approvals were obtained, a meeting was held in each hospital before the start of patient recruitment procedures. All documents required for the study are available at each participating site. The eCRF is a secure, interactive, web-response system available at each study center, provided and managed by the Biostatistics and Data Management Core Facility of Institut d’investigacions Biomèdiques August Pi i Sunyer (IDIBAPS) - Hospital Clínic, Barcelona.

In each participating Obstetrics Unit, the physicians and research personnel (research nurse or assistant) are in charge of patient screening and inclusion, ensuring compliance with the study protocol and collecting the study data in the eCRFs. The trial is being monitored by an independent monitor. The monitor regularly reviews the eCRFs, ensuring compliance with the trial protocol, data completeness and data accuracy. All adverse events and serious adverse events are being recorded according to standard procedures.

### Ethical considerations

The trial has been registered at European Clinical Trial Database (EUDRACT2012-000241-13) and at ClinicalTrials.gov (NCT01643980). The study is being conducted in accordance with Good Clinical Practice guidelines, the guiding principles of the Declaration of Helsinki, and applicable local regulations. The study was approved by the Spanish National Competent Authority (AEMPS) and by the Research Ethics Committees of the participating centers (listed in Appendix 3). Any relevant protocol amendments will be submitted to the competent Ethics Committee for review and will be updated in the trial registries. Participants are provided with information sheets and written informed consent is obtained prior to recruitment and baseline assessment.

A specific insurance policy has been contracted to cover compensations to patients in the event of injuries, in compliance with the requirements of Spanish law regarding clinical trials.

Although a third control arm with placebo is very valuable from a methodological point of view in a noninferiority comparative trial, it was discarded in our trial. The main reason was related to the fact that most participant hospitals were already treating these women with a short cervix (either with a pessary or with progesterone) as a measure to decrease the risk of preterm birth, based on recent publications. Although confirming data with regards to the superiority of both treatments versus placebo would have been highly valuable, it was considered ethically questionable.

## Discussion

Preterm birth is a major public health problem with a relevant neonatal morbimortality. It has been established that a short cervix (≤25 mm) diagnosed by transvaginal ultrasonography in the second trimester constitutes an important risk factor of preterm delivery [1, 9, 11, 39]. Although several therapeutic strategies (vaginal progesterone, cervical pessary and cerclage) have been used in these women showing a potential benefit, they have never been compared to one another in randomized trials. This study will assess the comparative efficacy of two of these three treatments (vaginal progesterone versus pessary). It is possible that the results of this study will contribute to the establishment of clinical recommendations regarding the use of both treatments in the prevention of preterm delivery in women with a short cervix.

## Abbreviations

CI: confidence interval
CMH: Cochran-Mantel-Haenszel
eCRF: electronic case report form
IDIBAPS: Institutd’investigacions Biomèdiques August Pi i Sunyer
ITT: intention to treat
ISCIII: Institute of Health Carlos III
PP: per protocol
RCT: randomized clinical trials
RR: relative risk
SCReN: Spanish Clinical Research Network
US: ultrasonography
USA: United States of America
